## Abstract

**Background:**

Chronic kidney disease affects more than 10% of the world’s population and is a non-communicable disease of global concern and priority. There is a significant implementation gap between best practice guideline recommendations and current kidney disease management. Previous research has shown the need to partner with primary care to improve education, collaboration, and kidney disease awareness. This implementation trial will explore use of an innovative clinical decision support software, Future Health Today, to improve screening, diagnosis, and management of kidney disease in primary care. The program will be supported by tertiary care outreach services. The primary aim is to test the hypothesis that the Future Health Today implementation program will improve screening, diagnosis, and management of kidney disease. Secondary aims are to evaluate primary care satisfaction and broader health service impacts.

**Methods:**

This pre-post implementation trial using an interrupted time series design will evaluate the clinical and service outcomes of Future Health Today, using a mixed methods study in twenty general practices with an estimated population size of 150,000. Deidentified patient data will be extracted from participating practices to examine the primary aims of the study. Surveys and semi-structured interviews with general practice will inform secondary hypotheses. Data linkage between primary care and tertiary care data will examine the broader health service impacts.

**Discussion:**

This investigator driven trial will assess the impact of Future Health Today software coupled with education and clinical outreach support. Investigators hypothesise that there will be improvement in appropriate screening, diagnosis, and management of kidney disease. This program has the potential to be scaled more broadly.

**Trial Registration:**

Australian New Zealand Clinical Trial Registry: ACTRN12623001096640.

**Supplementary Information:**

The online version contains supplementary material available at 10.1186/s12882-024-03489-y.

## Background

Chronic kidney disease (CKD) is estimated to affect more than 10% of the world’s population [1, 2]. There has been no improvement in global age standardised mortality rate from 1990 to 2017, despite significant improvements in other chronic conditions such as cardiovascular disease, cancer, and chronic obstructive pulmonary disease [3, 4]. Without fundamental improvements in care, CKD is estimated to be the 5th leading cause of years of life lost by 2040 [5].

A significant proportion of CKD is preventable owing to modifiable risk factors. Earlier detection and management can change the course of disease. The majority of CKD in Australia is diagnosed and managed in primary care, making this an important focus for quality improvement. A systematic review by Neale et al. identified common themes that were barriers to detection and management of CKD in primary care including time constraints, lack of knowledge or anxiety in providing a CKD diagnosis, and difficulty interpreting CKD guidelines [6]. They found technology and a collaborative approach were important enablers of improvement [6].

There has been significant work in Australia to utilize electronic clinical decision support systems to improve detection and management of CKD in primary care, in tandem with primary care education and improved collaboration with specialist services, however previous trials were limited by intensive resourcing, workflow integration and scalability [7, 8].

Future Health Today (FHT) is a clinical decision support and quality improvement software that has been developed by co-design with primary care physicians, practice nurses, hospital physicians and technology specialists, with the development and initial pilot previously published [9–11]. This trial aims to assess the clinical outcomes, clinician satisfaction and health services impacts of this new model of care incorporating FHT, education and outreach support.

### Ethics

Ethics approval for the Future Health Today implementation trial has been obtained from the Science, Technology, Engineering, Mathematics and Medicine ethics committee at the University of Melbourne 2023-27529-44500-3. Consent will be obtained at the level of the primary care practice. The ethics committee have approved a waiver of consent for the use of non-re-identifiable routinely collected patient data. Patients can opt-out of data collection by informing practice staff. The trial is registered with the Australia and New Zealand Clinical Trials Register (ACTRN12623001096640).

## Methods

### Study design

This will be a pragmatic implementation trial using an interruptive time series design comparing outcomes in the three years prior to trial commencement with three years of active trial. Primary care data will be linked with tertiary care administrative data to enable analysis of broader health service impact. The overall program evaluation will use a mixed methods approach using the clinical performance feedback intervention theory framework [12].

### Study population

This study will take place in twenty general practices in western Melbourne and will be supported by the local tertiary hospital. This is an area with high burden of chronic disease.

#### Inclusion criteria

Primary care practices in the western Melbourne catchment and their adult patients will be eligible for inclusion.

#### Exclusion criteria

Sites without the technical infrastructure to support the Future Health Today platform (the platform works with commonly used practice software Best Practice and Medical Director). Patients identified as having a renal transplant or dialysis will be excluded from the primary analysis.

#### Recruitment

 Recruitment will take place at the practice level and will focus on practices who have been identified to serve a patient population with a significant burden of chronic disease with complex care needs. These practices have been identified through a hospital program to support patients with high risk of hospital re-admission in the context of chronic disease. Recruitment will then be expanded to the broader tertiary centre catchment area as required.

### Intervention

A summary of the intervention is presented in Fig. 1. FHT software with kidney disease module and related cardiovascular disease and diabetes modules will be installed on primary care computers.

**Fig. 1 Fig1:**
[figure not shown]
Summary of intervention future health today implementation trial

Sites will be offered a software education session and provided with training videos (Supplemental appendix 1). Practices will also be provided a CKD education session (Supplemental appendix 2) and ongoing support by a nephrologist and nephrology nurse practitioner as required. During the trial practices will be encouraged to use the cohort function and complete quality improvement activities, commencing with screening patients at risk and providing a diagnosis to those with biochemical signs of CKD. Trial staff will assist practices by creating these initial cohorts.

Sites will be asked to nominate a practice champion. Practice champions will be a point of contact for the duration of the trial and asked to promote use of FHT at their practice site. They will also be providing survey and interview feedback at the end of year one and three, in addition to at least one primary care physician at the practice (Supplemental appendix 3–5).

Primary care data will be linked with tertiary centre records at baseline and then 6 monthly to end of the trial. Analysis of the retrospective cohort will be undertaken at baseline, with interim analyses yearly to end of trial. Yearly interim analysis will enable any program issues to be identified and addressed and identify areas where primary care practices may require further support. Evaluation of usability, feasibility and satisfaction will be undertaken at the end of year one and at the end of the trial.

### Outcomes

Primary outcome: change in the number of patients who are meeting quality of care indicators in three domains:

Screening: an appropriately timed kidney health check in patients at risk of kidney disease.Diagnosis: total number of patients with coded diagnosis of CKD.Management: patients with CKD on a renin angiotensin system inhibitors with at least 12 months follow up following a CKD diagnosis.

Secondary outcomes: these are divided into patient centric, health centric and overall evaluation.

Patient centric secondary outcomes:

1.1 Change in number of patients achieving the kidney cycle of care. This involves monitoring of renal function, albuminuria, diabetes (if diabetic), fasting lipids and blood pressure measurement.1.2 Change in proportion of patients on any antiproteinuric medication including angiotensin converting enzyme inhibitor (ACE inhibitor) or angiotensin receptor blocker (ARB), sodium glucose co-transporter 2 inhibitor (SGLT2 inhibitor) and mineralocorticoid antagonists (MRA). With sub analysis of each medication class.1.3 Change in proportion of patients with type two diabetes and CKD prescribed an SGLT2 inhibitor.1.4 Change in urinary albumin to creatinine ratio (uACR) in patients with CKD diagnosis and at least 12 months follow up.1.5 Change in slope of estimated glomerular filtration rate (eGFR) in patients with a coded diagnosis of CKD compared 2 years prior and 2 years post and adjusted for baseline function. The index date will be CKD diagnosis coded or if CKD already diagnosed at entry into study.1.6 Subgroup analysis: Subgroup analysis will be undertaken comparing those with a coded diagnosis of CKD, to those with measured CKD (all patients meeting CKD diagnostic criteria) and possible CKD (patients who have one eGFR or uACR in diagnostic criteria). This will be conducted as CKD is well known to be under coded in the medical health record. CKD will be defined according to the Kidney Disease Improving Global Outcomes criteria [13].1.7 Potential further subgroup analysis will be conducted with frequent, moderate, and minimal users of FHT (if a difference is found between practices).

Health centric secondary outcomes:

2.1 Change in referral patterns to tertiary services from practices participating in FHT.2.2 Change in pattern of late referrals to nephrology services. This will be benchmarked against the National average and tertiary centre average.2.3 Change in number of admissions to the tertiary centre with CKD being newly diagnosed in participating practices.

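### Primary outcomes are stated as patient numbers, and Diagnosis as an undenominated total of coded CKD, so list size and persisting codes mix into the result

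*Protocol article*

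**What the plan says.** The Outcomes section of the protocol article sets the scale of the primary outcome in its opening line: "change in the number of patients who are meeting quality of care indicators in three domains". The three domains are then given as follows.

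- Screening: "an appropriately timed kidney health check in patients at risk of kidney disease".
- Diagnosis: "total number of patients with coded diagnosis of CKD".
- Management: "patients with CKD on a renin angiotensin system inhibitors with at least 12 months follow up following a CKD diagnosis".

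Screening and Management each name a group that could serve as a denominator. Diagnosis names none and is not limited to new codes. Outcome 1.5 shows that patients coded before entry are expected among those with CKD: "The index date will be CKD diagnosis coded or if CKD already diagnosed at entry into study".

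The same section uses the other scale elsewhere. Outcome 1.2 is a proportion, and so is 1.3: "Change in proportion of patients with type two diabetes and CKD prescribed an SGLT2 inhibitor". Outcome 1.1 is a number, and so is 2.3: "Change in number of admissions to the tertiary centre with CKD being newly diagnosed in participating practices".

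The Data analysis section assigns the primary outcomes, described as nominal, a chi-square test of pre against post at the 0.05 level. Study design and Discussion describe an interrupted time series with three years on each side. The Discussion gives it the task of separating a natural rise in all three domains from an effect of the intervention.

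**The concern.** A number of patients can change for reasons unrelated to quality of care. If lists grow, every count grows with them. A code for a chronic disease normally stays in the record, so the coded total is a stock that rises whenever new coding outpaces deaths, departures and code removal. Management draws on that stock, because its patients need a CKD diagnosis and 12 months of follow-up after it.

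The Discussion itself names background improvement as the rival explanation, and an undenominated total adds list size to it. Outcome 2.3 carries a further risk: practices are encouraged to give a diagnosis to patients whose tests already suggest CKD, so the group whose admissions are counted may grow because the programme works. At stake is whether the primary result can be read as a change in care.

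**Working it through.** The article gives no sample size, baseline rate or list trend, so there is no stated figure to reproduce. What follows illustrates a world with no effect of the software.

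**Inputs from the article.** Population about 150,000 in twenty practices (Abstract; given as a population, not as adults); three years before and three years active, so period midpoints are three years apart; chi-square at 0.05.

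**Assumed inputs.** Coded CKD at baseline 2% (range 1 to 4%); net background coding of 0.2, 0.5 or 1.0 per 1,000 per year; list growth of 1 to 3% per year.

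**Step 1. List growth alone, coded prevalence constant at 2%.** Baseline count c0 = 150,000 × 0.02 = 3,000. Three years later c1 = 3,000 × (1 + g)³. A comparison of bare counts uses z = (c1 − c0)/√(c1 + c0), treating the two counts as independent.

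- g = 1%: c1 = 3,091 (+3.0%), z = 1.16, rejects 21% of the time.
- g = 2%: c1 = 3,184 (+6.1%), z = 184/√6,184 = 2.34, rejects 65%.
- g = 3%: c1 = 3,278 (+9.3%), z = 3.51, rejects 94%.

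A chi-square on proportions stays at 5% throughout. This is the part of the error that belongs to the count scale.

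**Step 2. Background coding alone, list constant.** With annual gain f, p1 = p0 + 3f and z = (p1 − p0)/√(2p̄(1 − p̄)/150,000), where p̄ is the mean of p0 and p1.

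- p0 = 2%, f = 0.2 per 1,000: 3,000 to 3,090 (+3.0%), rejects 21%.
- p0 = 2%, f = 0.5 per 1,000: 3,000 to 3,225 (+7.5%), z = 0.0015/0.00052 = 2.88, rejects 82%.
- p0 = 2%, f = 1.0 per 1,000: 3,000 to 3,450 (+15.0%), rejects more than 99%.
- f = 0.5 per 1,000 at other baselines: 98% at p0 = 1%, 55% at p0 = 4%.

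These are tests on proportions with a fixed denominator. They show what a pre-post test that ignores trend does, and a denominator does not cure it.

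**Step 3. Both together.** At p0 = 2%, f = 0.5 per 1,000 and g = 2%: 150,000 × 1.02³ × 0.0215 = 3,422, a rise of 14.1% with no effect.

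**Step 4. The promised design.** A segmented regression was fitted to noise-free monthly series (36 months before, 36 after) with the Step 3 inputs. On the proportion, the level change and the slope change are both 0. On the raw count, a spurious slope change of about +12 patients per year remains, on a base of 3,000.

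**Step 5. Outcome 2.3.** If it counts admissions among newly diagnosed patients, then admissions = n × r, with n the size of that group and r the admission rate per patient. If n is multiplied by k and r by m < 1, the count still rises whenever k × m > 1, although each patient is admitted less often.

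**The case against.** The strongest defence has three parts.

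First, describing the outcomes as nominal and naming a chi-square implies that each patient is classed as meeting the indicator or not. Screening and Management name their group, and exact denominators may sit in a full protocol or analysis plan that is not shown. This stands for those two domains: a chi-square can be formed for them. It does not rescue Diagnosis, for which no group is named. Nor does it explain why the primary outcome is worded as a number when 1.2 and 1.3 are worded as proportions. The scale is something the article states, not something it leaves open.

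Second, the interrupted time series would absorb a linear background trend, and Step 4 confirms that little would then remain even on counts. That is right about the design. But the Data analysis section gives the primary outcomes a pre-post chi-square and names no trend model for them; regression appears there only for covariate control.

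Third, outcome 2.3 is secondary and its wording is ambiguous. That also stands, so the point about it holds only under the reading used in Step 5.

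A reader might go further and infer that Diagnosis is nearly certain to show improvement with no effect. The documents do not support this. They give no baseline, coding rate or list trend; with background coding of 0.2 per 1,000 per year the test rejects 21% of the time at a 2% baseline and 13% at 4%; and counts fall if lists shrink. A reader might also infer that all three domains accumulate. Screening requires an appropriately timed check, which lapses, so it does not. Nor does the text say that Diagnosis counts everyone ever coded. It behaves as a stock only because codes usually persist.

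**Conclusion.** The concern holds in limited form. The primary outcome is fixed on a count scale, and Diagnosis is a total without a denominator. Followed as written, the result mixes list size, and for Diagnosis and Management the accumulation of codes, with any change in care.

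The part due to the count scale is about 3 to 9% over three years if lists grow 1 to 3% per year, which is an assumption. The larger false-positive rates (about 82% at a 2% baseline and 0.5 per 1,000 per year, 55 to 98% across baselines of 4 to 1%) come from the untrended pre-post test and would survive a change to proportions. Outcome 2.3 is open to the same kind of distortion under one reading of its wording.

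Because this concerns the primary outcome and the remedy is cheap, it should be settled before the pre-post comparison is made.

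**What to change.** State each domain as a proportion or rate, with one definition of an active patient and one denominator rule applied identically in every period.

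- Screening: the proportion of at-risk active adults with an in-date kidney health check.
- Diagnosis: the proportion coded among patients meeting the measured-CKD criteria of outcome 1.6, and/or new CKD codes per 1,000 uncoded active adults per month.
- Management: the proportion on a renin-angiotensin system inhibitor among patients with measured CKD and the required follow-up. Measured CKD is preferable because the intervention's coding directly enlarges a coded denominator. More testing could still bring patients into the measured group, so report its size over time.
- Outcome 1.1: a proportion.
- Outcome 2.3: an admission rate among patients with measured CKD.

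Make the interrupted time series of Study design and Discussion the primary analysis of these series, in place of the pre-post chi-square. The two changes belong together: the denominator removes the list-size part and the trend model removes a linear background rise.

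The cost is outcome and analysis wording, and a registry update if the outcomes are registered as counts. No new data are needed. Headline numbers would look less striking, but counts can still be reported descriptively.

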### Data analysis

Descriptive statistics will be used to describe the baseline characteristics in the historical control and active group. Primary end points will be calculated, and a chi square test will be used to assess if the difference between pre and post-test is significant for the primary outcomes (nominal data), with *p* < 0.05 considered significant.

Univariate analysis will be undertaken for each of the outcomes to compare differences in the characteristics of the historical control versus the three year active intervention. For continuous variables, the data will be tested for normality using Shapiro Wilk test and equality of variances using Levene’s test. If these assumptions hold true, parametric tests like the t-test or ANOVA will be used. If these assumptions do not hold then nonparametric alternatives will be considered. For categorical variables a Chi Squared test will be used. When comparing multiple groups, post hoc investigations may be included with Bonferroni corrections. Regression models will be used to control for co-variates.

The analysis will be undertaken 3 years prior to study commencement (historical control) and then interim analysis yearly until trial conclusion.

Survey responses will be analysed to understand the usability of FHT software and if practice staff felt the software aided their management of CKD. Semi structured interviews of practice champions and additional primary care physicians will be conducted via zoom or phone, according to interviewees preference. Interview transcripts will be coded by at least two researchers. The clinical performance feedback intervention theory framework will be used for the overall implementation evaluation combining survey and interview data [12].

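### If the targeted drugs cause an early eGFR drop, the single two-year post-index slope in outcome 1.5 may dilute, cancel or reverse an apparent benefit

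*Protocol article*

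**What the plan says.** The Outcomes section of the protocol article fixes four things about outcome 1.5.

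- Measure and windows: "Change in slope of estimated glomerular filtration rate (eGFR) in patients with a coded diagnosis of CKD compared 2 years prior and 2 years post".
- Adjustment: "adjusted for baseline function".
- Split point: "The index date will be CKD diagnosis coded or if CKD already diagnosed at entry into study".
- Population: patients whose CKD is coded.

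The same section makes prescribing a target in three places.

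- The Management domain of the primary outcome counts "patients with CKD on a renin angiotensin system inhibitors with at least 12 months follow up following a CKD diagnosis".
- Outcome 1.2 is "Change in proportion of patients on any antiproteinuric medication", covering ACE inhibitors or ARBs, SGLT2 inhibitors and MRAs.
- Outcome 1.3 is "Change in proportion of patients with type two diabetes and CKD prescribed an SGLT2 inhibitor".

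The Data analysis section adds in general terms that "Regression models will be used to control for co-variates" and names no covariates. The Study design section describes "comparing outcomes in the three years prior to trial commencement with three years of active trial", with no concurrent control group.

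The article does not mention an early eGFR drop on starting any of these drugs. It gives no eGFR measurement schedule, expected uptake, start times or expected slope benefit.

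**The concern.** One slope per window cannot tell a single downward step from a steady decline. If starting a targeted drug lowers eGFR once and early, a start after the index date makes the post-index slope steeper even when the underlying rate of loss is unchanged.

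The exposure is lopsided by design. The Intervention section says practices begin with screening and with giving a diagnosis to those who have biochemical signs of CKD. A program that works should therefore produce drug starts after coding, which is the post-index side. Adjusting for baseline eGFR does not remove a step that comes after baseline, and no concurrent control group would share the step and cancel it.

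Outcome 1.5 is the listed outcome that follows the rate of change in kidney function. A real benefit could be understated, or even appear as a loss, because prescribing improved.

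**Working it through.** The article gives no slope, standard deviation, sample size or drop size for outcome 1.5, so there is no figure to reproduce. Everything below is an illustration.

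**Inputs**

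- From the article: a 2-year post-index window, one slope per window, and three targeted drug classes.
- Assumed: a least-squares line; eGFR at 0, 0.5, 1, 1.5 and 2 years with the index value included; drop D of 2 to 4 mL/min/1.73m2; new starters u of 15% to 30%; slowing of later decline b, varied.

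**Step 1: effect of a step on the slope.** The mean time is 1 and the sum of squared deviations is 1 + 0.25 + 0 + 0.25 + 1 = 2.5. The weights (t - 1)/2.5 are therefore -0.4, -0.2, 0, 0.2 and 0.4. The coefficient k of a unit step is the sum of the weights from the first affected value onward.

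- First affected value at 0.5 years: -0.2 + 0 + 0.2 + 0.4 = 0.4
- At 1 year: 0 + 0.2 + 0.4 = 0.6
- At 1.5 years: 0.2 + 0.4 = 0.6
- At 2 years: 0.4

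**Step 2: shift per new starter**, k × D. For D = 3 this is 0.4 × 3 = 1.2 to 0.6 × 3 = 1.8 mL/min/1.73m2 per year of apparent extra decline.

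**Step 3: shift in the cohort mean**, u × k × D, with b = 0.

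- D = 3: 0.15 × 1.2 = 0.18 to 0.30 × 1.8 = 0.54 per year
- D from 2 to 4: 0.15 × 0.4 × 2 = 0.12 to 0.30 × 0.6 × 4 = 0.72 per year

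**Step 4: allow for true slowing.** The net change in mean slope is u × (-kD + hb), where h is the share of the later slowing that the fitted line picks up. The break-even b per 1 mL of drop is k/h. Starts are placed 0.01 year after the time shown.

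| Start after index | k | h | Break-even b per 1 mL of drop |
|---|---|---|---|
| 0 | 0.40 | 0.996 | 0.40 |
| 6 months | 0.60 | 0.794 | 0.76 |
| 12 months | 0.60 | 0.494 | 1.21 |
| 18 months | 0.40 | 0.196 | 2.04 |
| Evenly spread | 0.50 | 0.50 | 1.0 |

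For D = 3, a true slowing of 0.40 × 3 = 1.2 per year (start just after index) to about 1.0 × 3 = 3 per year (starts evenly spread) is needed merely to show no change.

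**Step 5: the sign can go either way.** At u = 50%, an illustrative uptake above the range in Step 3:

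- Start just after index, D = 3, b = 1: 0.5 × (-1.2 + 0.996) = -0.10
- Same start, D = 3, b = 1.5: 0.5 × (-1.2 + 1.494) = +0.15
- Same start, D = 2, b = 1: 0.5 × (-0.8 + 0.996) = +0.10
- Start at 12 months, D = 3, b = 1: 0.5 × (-1.8 + 0.494) = -0.65

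Uptake u multiplies the whole bracket, so it scales the net change but does not set its sign.

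**Step 6: sensitivity.** With 3-monthly values k runs from 0.27 to 0.67 for the start times in the table; with annual values it is 0.50. With continuous measurement k = 6f(1 - f)/2, where f is the start time as a fraction of the window, with a maximum of 0.75 at mid-window. If the drug starts just after index and the index value is left out, k = 0. A start in the 2 years before index puts the step in the pre-index slope, making that slope steeper and biasing the change towards benefit.

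**The case against.** Three objections carry weight.

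1. **The model is not stated.** The article does not name least squares, and the unnamed covariates in the Data analysis section could include drug start. A full protocol or analysis plan may specify the slope model. This limits the point, but the article does fix the measure, the windows, the split point and one adjustment. Baseline adjustment cannot remove a later step, and a general promise of covariates does not commit to a term that would.

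2. **The drop is not in the documents.** Its existence, timing and size are assumptions, as are uptake and the measurement schedule. This stands in full, and every figure is conditional on it.

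3. **Total slope is a coherent quantity.** It describes net eGFR change, including any early loss. A slope that models around drug start conditions on an event the program itself tries to change. This also stands, and is why the total slope should not be replaced.

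A reader might infer more: that success on prescribing will register as faster decline, or that more prescribing always makes 1.5 look worse. The documents support neither. They give no drop size, slowing or start times, and Steps 5 and 6 show that plausible-looking combinations read as better, as worse, or as biased towards benefit.

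**Conclusion.** The point holds in conditional form. As defined, outcome 1.5 mixes any one-off eGFR change at drug start with the later rate of loss, in a program meant to increase such starts after diagnosis. Under the assumed drops, starter shares and 6-monthly schedule, the mean post-index slope shifts by -0.12 to -0.72 mL/min/1.73m2 per year before any true slowing. That may dilute, cancel or reverse an apparent benefit; the direction of the net result cannot be settled from the article.

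The consequence is moderate. This is one secondary outcome, and the article ties no success criterion or stopping rule to it. The change is still worth making, because the present definition cannot separate two explanations of a steeper slope.

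**What to change.** Keep the total slope in outcome 1.5 as defined. Beside it, pre-specify one companion analysis in either of two forms:

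- a level-shift term at the first start of any targeted class (RAS inhibitor, SGLT2 inhibitor or MRA), whether the start falls in the pre-index or the post-index window; or
- omission of eGFR values from the first 3 months after a start, with the level allowed to differ before and after.

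Report the two slopes together, and state in advance that a steeper total slope alone will not be read as faster progression. Including starts in both windows matters, because pre-index starts bias the change the other way.

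The cost is a few lines of analysis text and one model term. Prescribing and eGFR are already needed for other outcomes and come from the primary care record, so no new data source should be required, provided the extract carries dates. The companion slope will have slightly wider intervals. Because it conditions on a post-index event, it supplements the total slope and does not replace it.
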